**Fig. 1 Fig1:**
[figure not shown]
Timeline of the PROBIA study

### Randomization and study intervention

After eligibility checks have been conducted and written consent has been obtained by the different psychiatrists and/or psychologists of the trial team, eligible participants will be randomized to the experimental (EG) or the control (CG) group in a 1:1 allocation ratio using an independent web-based computerized service (www.randomization.com). Randomization will be center-stratified and have a fixed length per center, being independent of participant characteristics. However, due to the large sample size, a balanced ratio of baseline characteristics between the EG and CG is expected.

Individual participant treatment kits will contain all required daily synbiotic or placebo envelopes for the 10-week RCT and will be prepared in advance by sequentially numbering and labeling them as “A” or “B.” Because this is a double-blind study, neither the participants nor the clinicians involved in the trial will have access to the randomization list.

Synbiotic 2000 Forte 400 (SF) is a synbiotic formula currently produced by Synbiotic AB in Höganäs, Sweden. Each dose (powder-containing sachet) of SF contains 100 billion of each of *Pediococcus pentosaceus* 5-33:3, *Lactobacillus paracasei subsp. paracasei* 19, *Lactobacillus plantarum* 2362, and *Leuconostoc mesenteroides* 77:1, in combination with four bioactive fermentable fibers (2.5 g each of β-glucan, inulin, pectin, and resistant starch). SF is categorized as a generally regarded as safe agent, being tested on several hundreds of critically ill patients (e.g., pancreatitis, liver transplant) with no side effects or specific and/or relevant risks conferred to the trial participants [83]. The placebo (also provided by Synbiotic AB) is composed of the polysaccharide maltodextrin and has a texture and flavor similar to SF. Participants will be asked to continue with their previous medications and/or usual treatments and add the synbiotic or placebo once daily on top of cold foods such as yogurt, muesli, or salad. To secure bacterial viability, participants will be asked to store both SF and placebo at + 4–6 °C.

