Recruitment began on 22 February 2019 and will have a duration of 2 years. A total of 180 participants (60 subjects per site) will be recruited by trained psychiatrists and/or psychologists at the different sites (see Fig. 1). Strategies aimed at optimizing the recruitment process will include the distribution of handouts or flyers to colleagues, physicians, and families, as well as an offer of reimbursement of study-related travel costs to participants. Furthermore, and depending on local regulations, information via presentations, websites, and social media campaigns will be provided. Regular calls will be made to patients to avoid participant withdrawal from the study.

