### Outcome measures

#### Primary outcomes

The primary outcome measure will be response to treatment, defined by a reduction in the Affective Reactivity Index–Self-Report (ARI-S) scale total score of at least 30% compared with baseline plus a Clinical Global Impression–Improvement Scale total score of 1 or 2 (very much improved or much improved) at the end of the placebo-controlled phase.

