### Study monitoring

Proper conduct of data collection in the trial will be monitored via on-site visits of a monitoring staff member throughout the study; quality of data collected will further be monitored regularly by a statistical supervision team. After the first five participants per site are included, the quality of data (on item/trial level) per participant will be checked, aiming at detecting any error that may occur in the beginning of the project and to prevent these errors from recurring. After including participant numbers 5 to 10, the completeness and accuracy of the data on summary/scale level will be checked for all participants. Thereafter, data on a summary/scale level will be checked randomly for 1 in 5 participants. Outcomes of this data check will be written in an overview and reported to all research personnel. If adjustments to the database or procedures need to be made, these will be made as soon as possible. Moreover, the investigators will permit quality data checks, audits, and inspections by providing the sponsor direct access to source data and other documents (e.g., medical files) by request.

In each participating center, the PI will be responsible for the local ethics application, on-site training of clinicians, identification and recruitment of participants including randomization, data collection according to the study protocol, completion of the case report forms including answering queries, maintaining and updating the investigator site file, participation in monitoring, and reporting SAEs to the study PI in Barcelona. Each site will have regular meetings with their clinical team in order to ensure progress of the trial. As the leading coordinator center and with the aim of monitoring the study progress, the VHIR team will arrange telephone meetings with the local sites throughout the project on a regular basis.

Due to the need for research groups to share their data to maximize the value of each research contribution, to pool them to address research questions that require larger numbers, or to carry out meta-analyses, participants and, if applicable, their legal guardians will be asked whether they consent that their data (or portions of their data) will be shared in anonymized fashion with other research projects.

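### All kits share one of only two letters, A or B, so learning one participant's treatment decodes every participant under that code

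*Protocol article*

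**What the plan says.** All quotes are from the protocol article.

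- **Kits** (Randomization and study intervention): "Individual participant treatment kits will contain all required daily synbiotic or placebo envelopes for the 10-week RCT". They "will be prepared in advance by sequentially numbering and labeling them as" A or B.
- **Safeguard** (same section): "neither the participants nor the clinicians involved in the trial will have access to the randomization list". The section mentions no unique kit code, no cover over the letter, and no change in the meaning of the letters between centers.
- **Allocation** (same section): participants are allocated "in a 1:1 allocation ratio using an independent web-based computerized service". "Randomization will be center-stratified and have a fixed length per center, being independent of participant characteristics".
- **Numbers** (Study population and recruitment): "A total of 180 participants (60 subjects per site) will be recruited by trained psychiatrists and/or psychologists at the different sites".
- **Site duties** (Study monitoring): the site's principal investigator answers for "identification and recruitment of participants including randomization, data collection according to the study protocol".
- **Endpoint** (Primary outcomes): response needs a fall of at least 30% in the self-reported ARI-S and also a "Clinical Global Impression–Improvement Scale total score of 1 or 2 (very much improved or much improved").
- **Visits** (Table 3): the Bristol Stool Scale and the side-effect questions are collected at T1 and T2, as is the CGI-I.

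**The concern.** A label that takes only two values in a two-arm trial is a group label. It does not name the product, but it tells anyone who can read it which participants are treated alike. Two things follow.

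First, the blind of all participants depends on each single one. Once somebody learns what one participant received, the letter on that kit carries the knowledge to everyone else.

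Second, weak clues add up. A rater who cannot tell from one patient whether the sachet is active can compare all A patients with all B patients. The active sachet holds four fermentable fibers at 2.5 g each, 10 g per dose, and the placebo is maltodextrin. If that produces any visible difference in gastrointestinal symptoms, the shared letter makes it usable.

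What is at stake is the primary comparison. Both components of response, a self-report and a global impression, are open to expectation. Bias from a lost blind cannot be removed at analysis.

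**Working it through.** The plan gives no figure on this point, so there is nothing to reproduce. The check has four steps.

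**1. Allocations exposed by one disclosure.** Inputs: 180 participants, 60 per site, two arms, two letters. Suppose one participant with an A kit is found to be on product X. Then A = X, and by elimination B = the other product.

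| Coding | Allocations known after one disclosure |
|---|---|
| Two letters, same meaning at all centers | 180 of 180 (100%) |
| Two letters, meaning differs by center | 60 of 180 (33%) |
| Unique kit numbers unrelated to arm | 1 of 180 (1/180 = 0.6%) |

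This does not depend on the order of dispensing. It needs only that the letter on each issued kit can be read or is recorded.

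**2. Pooling of clues.** With 60 per site and 1:1 allocation, each center can compare about 30 A participants with about 30 B participants. The stool scale, the side-effect questions and the CGI-I fall at the same visits (T1, T2). Under Criteria for discontinuing allocated interventions, adverse events are also asked about at each visit and discussed with the site's study physician. With unique numbers each participant is a group of one, and no such comparison can be made.

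**3. Predictability of the next letter (conditional).** If kits are used in number order and the letter is legible on stock held at the site, the next letter is known with certainty instead of with 50% probability. If only past letters are known, a simulation (1:1, 60 per center, always guess the less-used letter, 20,000 runs) gives these proportions of correct guesses. The article states no block size, so block size is an assumption.

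| Assumed list structure | Correct guesses |
|---|---|
| One balanced list of 60 | 57% |
| Blocks of 10 | 65% |
| Blocks of 6 | 68% |
| Blocks of 4 | 71% |

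**4. Illustration of type I error.** Assume no true effect, 20% response (the article's control rate), 90 per arm, and a two-sided pooled z-test at 0.05. Assume also that decoded letters raise response in one arm and lower it in the other by s points. The critical difference is 1.96 × √(2 × 0.20 × 0.80 / 90) = 1.96 × 0.0596 = 0.1169.

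- s = 2.5 (17.5% v 22.5%): SE = √[(0.175 × 0.825 + 0.225 × 0.775)/90] = 0.0595. Upper tail: Φ((0.05 − 0.1169)/0.0595) = Φ(−1.12) = 0.131. The lower tail adds 0.003. Total about 13%.
- s = 5 (15% v 25%): SE = √[(0.15 × 0.85 + 0.25 × 0.75)/90] = 0.0592. Upper tail: Φ((0.10 − 0.1169)/0.0592) = Φ(−0.29) = 0.388. The lower tail is negligible. Total about 39%.

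A simulation of 200,000 trials gave 13.1% and 38.7%. The shifts are chosen for illustration and do not come from the documents.

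**The case against.** A reader might infer that the labels reveal each next allocation, that withholding the list therefore conceals nothing, and that the trial is not double-blind. The text does not support these stronger readings.

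- **Next allocation.** The article does not say that kits are dispensed in number order, that A and B are mixed in one series, that recruiters hold unallocated stock, or that the letter can be read from outside. The wording also fits numbering within each letter, with the web service naming the kit. In that case the labels predict nothing. Preparation in advance, sequential numbering and one kit per participant make the first reading natural, but it remains an inference. The point on the next letter is therefore conditional.
- **Letter versus product.** Until it is decoded, a visible A shows the group and not the treatment, and the list stays withheld. Foreseeing a letter gives no informed basis for selecting or rating patients before then. This stands.
- **Triggers.** The article sets reporting times for unexpected serious reactions but describes no code break. It reports no side effects in earlier use and a placebo of similar texture and flavor. It does not show that the arms can be told apart by symptoms. A participant's own symptoms could also unblind that participant under any labelling. What the shared letter adds is the spread to others, and the likelihood of a trigger cannot be computed from the article.
- **Size of bias.** The shifts in step 4 are averaged over all 180 participants, as if decoding came before nearly every T2 rating. A later break would bias only later ratings. A biased CGI-I alone cannot create a responder, because the ARI-S criterion must also be met.

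These objections do not remove the central point. The article states the two-letter label as the procedure, so the point does not rest on missing detail, and nothing stated there limits a disclosure to one participant.

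**Conclusion.** The concern holds as a weakness in the stated blinding procedure. One disclosure or correct inference exposes 180 allocations, or 60 if letter meanings differ by center, instead of 1, and withholding the list does not change that. This rests on two things: that there are only two codes, which is stated, and that the letter on an issued kit is readable or recorded, which the label implies and nothing in the article contradicts. Exposure of the next letter before enrolment is possible but conditional on dispensing order and legibility. The figures of 13% and 39% show how sensitive the test is to biased response and do not estimate bias in this trial. The documents do not show that blinding or allocation concealment has failed. They show that the stated procedure does not contain a breach if one occurs.

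**What to change.** For every kit not yet issued:

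1. Replace the A/B letter with a unique, non-informative kit number that is not in allocation order.
2. Hold the number-to-arm key with the independent randomization service or the supplier, away from the sites.
3. Make code breaks participant-specific, so that one break reveals one allocation.
4. Record how many lettered kits had already been issued, by center.

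The cost is relabelling the remaining stock and one new code list. Sample size and treatment are unchanged. Kits already issued cannot be changed. The article, published in February 2020, expected recruitment to end on 1 April 2021, so part of the stock could still be relabelled at publication. If the full protocol already masks the letter or varies its meaning by center, the article's description should be corrected to say so. Variation by center alone would still leave 60 allocations exposed to one break.

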### Outcome measures

#### Primary outcomes

The primary outcome measure will be response to treatment, defined by a reduction in the Affective Reactivity Index–Self-Report (ARI-S) scale total score of at least 30% compared with baseline plus a Clinical Global Impression–Improvement Scale total score of 1 or 2 (very much improved or much improved) at the end of the placebo-controlled phase.

#### Secondary outcomes

The secondary outcome measures are selected to assess intervention effects on symptoms of impulsivity, compulsivity, and aggression via a series of selected scales and questionnaires (e.g., the Strengths and Difficulties Questionnaire, Yale-Brown Obsessive Compulsive Scale, Difficulties in Emotion Regulation Scale, and the Urgency, Premeditation [lack of], Perseverance [lack of], Sensation Seeking, Positive Urgency, Impulsive Behavior Scale [UPPS-P]). Interestingly, the UPPS-P consists of a 59-item self-report assessing five subscales (negative and positive urgency, premeditation, perseverance, and sensation seeking), with a mean value being calculated separately for each scale, allowing the estimation of distinct dimensions of impulsive behavior [84]. Another secondary outcome measure will be the change in ADHD symptoms (via the ADHD Rating Scale [ADHD-RS]). Like the UPPS-P, the ADHD-RS provides not only a total ADHD score but also separate scores for inattentive, hyperactive, and impulsive subscales, providing a better characterization of patients.

Changes in general psychopathology, major stressors, neurocognitive function, sleep disturbances, body-related measures (e.g., pulse rate, blood pressure, body mass index, waist–hip circumference ratio), medications taken, physical activity (via mobile health application and movement sensors), health-related quality of life, microbiome composition, and blood markers will also be evaluated. Blood markers will include genetic parameters, hormones, neurotransmitters, nutrients, and inflammatory/anti-inflammatory molecules (see Table 2).

**Table 2 Tab2:** Measurement of blood markers

Type of marker	Marker name	Link with:	Tissue
Inflammation	TNF-α	Inflammation/exercise*/diet	Serum/plasma
	IL-1β	Inflammation/exercise*/diet	Serum/plasma
	IL-6	Inflammation/exercise*/diet	Serum/plasma
	CRP	Inflammation/diet	Serum/plasma
	Bacterial lipoprotein	Inflammation/diet	Serum/plasma
	Vitamin B_12_	Diet	Serum/plasma
	Folic acid	Diet	Serum/plasma
Vitamins and minerals	Vitamin D	Diet	Serum/plasma
	Iron	Diet	Serum/plasma
	Cu	Diet	Serum/plasma
Nutrients	Cholesterol	Diet	Serum/plasma
	Glucose	Diet	Serum/plasma
	Homocysteine	Diet	Serum/plasma
	BDNF	Diet	Serum/plasma
	5-HT	Diet	Serum/plasma
Other markers	SCFA	Diet	Feces
	GLP-1	Hormone-diet	Serum/plasma
	Insulin	Hormone-diet	Serum/plasma
	Paraoxonase	Diet	Serum/plasma

*Abbreviations: 5-HT* serotonin, *BDNF* brain-derived neurotrophic factor, *CRP* C-reactive protein, *GLP-1* glucagon-like peptide 1, *IL* interleukin, *SCFA* short-chain fatty acid, *TNF-α* tumor necrosis factor-α

Blood samples (34.5 ml) will be fractioned into serum and plasma and stored at − 80 °C. Then, they will be shipped to the Department of Human Genetics of Radboudumc, Nijmegen, The Netherlands, for storage. Thereafter, blood markers will be measured at the Department of Clinical Biochemistry at Radboudumc in Nijmegen according to validated protocols. Participants willing to take part in the assessment of their microbiome will receive a specially designed container for feces collection, allowing participants to send the samples by ordinary post to the individual centers, where they will be processed and stored at − 80 °C for later shipping to the Department of Human Genetics of Radboudumc for sequencing and analysis of bacterial DNA. Crucially, before and during the intervention, the participants will be asked to send back their fecal samples within 24 h after the test sessions.

Another secondary outcome measure will be the change in nutritional intake. Participants will be asked to complete at least three 24-h dietary recalls (24HDRs): at baseline, during the intervention, and directly afterward, including two weekdays and one weekend day on nonconsecutive days. They will need to describe the type and amount (in grams) of all drinks and foods consumed during the previous days, starting with the first intake after waking up in the morning. Moreover, they will have to specify the time for every meal occasion during the day (breakfast, lunch, dinner, or snack).

Participant compliance with the intervention (SF or placebo) will be monitored with the Probabilistic Medication Adherence Scale throughout the 10 weeks of the intervention. Moreover, participants will be asked to return unused envelopes from the previous visit. This will enable us to secure bacterial viability and at the same time estimate adherence to treatment. Finally, the presence of somatic complaints/side effects or gastrointestinal symptoms (via the Bristol Stool Scale) will also be evaluated.

### Participant timeline

The trial timeline is shown in Table 3. Time points per intervention will be selected on the basis of known duration to exert effect.

**Table 3 Tab3:** Standard Protocol Items: Recommendations for Interventional Trials (SPIRIT) schematic schedule of enrollment, interventions, and assessments

Study procedures		Screening	Open label			Follow-up
	Visit	TS	T0	T1	T2	T3
	Week	−1	1	5	10	11
	Day	−7 to −1	1	35 ± 2	70 ± 2	77 ± 2
Informed consent form		X				
Inclusion/exclusion criteria		X				
Demographics (including SES)		X				
IQ (IQ score based on WAIS, if available)		X				
M.I.N.I.-Plus assessment		X				
Confirmation of diagnosis/-es		X				
Confirmation of ADHD	DIVA 2.0	X				
Confirmation of BPD	SCID-II	X				
Primary outcome						
Clinical Global Impression–Improvement Scale	CGI-I			X	X	X
Affective Reactivity Index	ARI-S	X	X	X	X	X
Secondary outcomes						
Clinical Global Impression–Severity Scale	CGI-S	X	X	X	X	
Clinician rating of ADHD symptoms	ADHD-RS		X	X	X	
Self-rating of multidimensional impulsivity	UPPS-P		X	X	X	
Questionnaire on well-being			X		X	
Functioning Assessment Short Test	FAST		X	X	X	
Self/other rating of strength and difficulties	SDQ		X	X	X	
Clinician rating of compulsivity	Y-BOCS		X	X	X	
Sleep problems	5-item questionnaire		X	X	X	
Self-rating of emotion regulation difficulties	DERS-16		X	X	X	
Somatic complaints/side effects	Body system questions			X	X	X
Gastrointestinal symptoms	Bristol Stool Scale		X	X	X	X
Self-rating of perceived stress	PSS		X	X	X	
Major stressors			X	X	X	
Blood pressure, pulse rate, height, weight, waist, hip, medical history, medication evaluation	Assessed by clinician		X	X	X	
Physical activity	Actigraphy; mobile health application		X		X	
Blood biomarkers	Blood sample		X	X	X	
Microbiome	Stool sample		X	X	X	
DNA and RNA	Blood sample		X	X	X	
Neurocognitive measures	CPT-II		X	X	X	
Nutritional intake	Food diary		X	X	X	
Treatment adherence/satisfaction/beliefs						
Probabilistic Medication Adherence Scale	ProMAS		X	X	X	

*Abbreviations: ADHD* attention-deficit/hyperactivity disorder, *ADHD-RS* Attention-Deficit/Hyperactivity Disorder Rating Scale, *ARI-S* Affective Reactivity Index–Self-Report, *BPD* borderline personality disorder, *CGI-I* Clinical Global Impression–Improvement Scale, *CGI-S* Clinical Global Impression–Severity Scale, *CPT-II* Continuous Performance Test, *DERS-16* Difficulties in Emotion Regulation Scale, *DIVA 2.0* Diagnostic Interview for Adult ADHD, Second Edition, *FAST* Functioning Assessment Short Test, *IQ* intelligence quotient, *M.I.N.I.-Plus* Mini-International Neuropsychiatric Interview, *PROBIA* Treatment of impulsivity in adults with probiotics, *ProMAS* Probabilistic Medication Adherence Scale, *PSS* Perceived Stress Scale, *SCID-II* Structured Clinical Interview for DSM-IV Axis II Disorders, *SDQ* Strengths and Difficulties Questionnaire, *SES* socioeconomic status, *UPPS-P* Urgency, Premeditation (lack of), Perseverance (lack of), Sensation Seeking, Positive Urgency, Impulsive Behavior Scale, *WAIS* Wechsler Adult Intelligence Scale, *Y-BOCS* Yale-Brown Obsessive Compulsive Scale

At the screening visit (TS), the rate of impulsivity will be established by performing structured interviews, the ARI-S, and the Clinical Global Impression–Severity Scale. After having established the presence of high impulsivity, the diagnosis of ADHD and/or BPD will be assessed via the Diagnostic Interview for Adult ADHD, Second Edition, and the Structured Clinical Interview for DSM-IV Axis II Disorders section for BPD, respectively. Thereafter, screening for eligibility based on clinical history, demographics (including SES), tests, and questionnaires (e.g., Mini-International Neuropsychiatric Interview [M.I.N.I.-Plus], IQ tests [Wechsler Adult Intelligence Scale, Fourth Edition]) will be performed, and informed consent will be obtained. Once this process is finished, a mobile health system as well as a food record will be introduced to participants (duration, approximately 1 h). The mobile health system will enable patients to share (via a mobile application) data of interest regarding their physical activity (acceleration, number of steps).

Trial-specific assessments will be done at T0 (duration, approximately 3 h), scheduled within 1 week after TS. During the week between TS and the baseline visit (T0), the mobile health system will be used at home. Here and during 24 h, participants will wear movement sensors on two working days and on Saturday and Sunday, and they will be asked to complete three 24HDRs on a web-based tool or paper on two nonconsecutive weekdays and one weekend day (duration, 15 min each). Individuals will also be asked to collect feces on one day during the 1-week period at home and to bring it along at T0.

In addition to responding to the questionnaires and scales listed in Table 1, participants will be instructed on how to store and eat the study product (SF or placebo). The intervention will begin on the day after T0, and participants will be asked to continue with their usual medications and/or treatments. Participants will have to complete another three 24HDRs, collect their feces before the next visit, and bring it along at T1, following the same guidelines as during the screening assessments.

T1 (midintervention assessment; duration, approximately 3 h) will take place 5 weeks after T0. This midintervention assessment aims at obtaining the primary and secondary outcome measures during the ongoing trial. Participants will be asked once again to wear movement sensors, complete another three 24 HDRs, and collect their feces 1 week before T2 and bring it along at T2. At 10 weeks after initiating the probiotic or placebo intervention (T2), primary and some secondary outcome measures will be assessed again (duration, approximately 3 h).

Within 1 week after T2 and with the aim of measuring safety aspects of the intervention (i.e., somatic complaints/side effects as well as gastrointestinal symptoms), the follow-up (T3) assessment will take place (duration, approximately 20 min).

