### Gut microbiome, microbiota, and behavior

Although *microbiota* refers to the specific microorganisms that are found within a specific environment, *microbiome* refers to the collection of genomes from all the microorganisms found in this particular environment [24]. It is hypothesized that an imbalance in the gut microbiota (dysbiosis) may have a negative effect on neurodevelopment, behavior, and cognition [25–31]. Related to this, changes in human microbiome and/or microbiota composition have been consistently found in individuals with autism spectrum disorder (ASD) [32–36], and a pilot study on the microbiome has demonstrated, for the first time, a difference in several bacterial taxa between subjects with ADHD and healthy control subjects [37]. Specifically, lower *Firmicutes* genus and higher *Bifidobacterium* genus were found in subjects with ADHD than in healthy individuals, with the increase in the *Bifidobacterium* genus relating to decreased ventral striatal functional magnetic resonance imagining responses during reward anticipation [37].

The relationship between gut microbiota and the brain seems to be bidirectional. The gut microbiota modulates brain function and development, and the brain can alter the gut microbiota, allowing colonization by pathogenic bacteria [38–40]. Illustrating this idea, some studies have shown an overrepresentation of gastrointestinal symptoms in patients with both neurodevelopmental and neuropsychiatric disorders [41–48], and a study in healthy students found that during exams, psychological stress increased at the same time that numbers of lactobacilli in stool samples decreased [49].

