### Statistical analysis

Primary outcome measures will be analyzed by applying logistic regression analyses with type of treatment, diagnostic group (e.g., ADHD, BPD, or both), gender, and center as independent variables. A sample size of 180 participants will allow for detection of an odds ratio of 2.55 with 90% power, assuming a response rate of 20% for the CG at a significance level of 0.05. For simplification purposes, calculations will assume no effects of the covariates on the response rate. Secondary analyses will be performed on the secondary outcome measures assessed at the different time points. General linear models will be applied to examine effects of treatment group on continuous outcome variables while controlling for baseline assessment, gender, diagnostic group, and center. Categorical outcome measures will be investigated using generalized linear models. Treatment effects and their 95% confidence intervals will be reported. To investigate potential long-term effects of probiotics, data of the EG for 10 weeks will be analyzed. General linear models for repeated measurements will be applied to study changes from baseline to follow-up visit for this group, and missing data will be handled by the last observation carried forward method. Statistical significance will be defined at the 0.05 level.

Once the primary and secondary outcome measures results are obtained, all responsible investigators at all study sites will get access to the data to be able to reanalyze the data regarding specific additional research questions.

In case of an external request for replication, the respective statistical analysis will be provided by the trial statistician.

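### Somatic complaints/side effects, one of two safety aspects named for T3, are the only secondary outcome in Table 3 without a T0 assessment

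*Protocol article*

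**What the plan says.** In the protocol article, Table 3 (section Participant timeline) lists "Somatic complaints/side effects" as a secondary outcome, measured by "Body system questions", with marks at T1, T2 and T3 and blanks at screening and T0. The next row, "Gastrointestinal symptoms", measured by the Bristol Stool Scale, is marked at T0, T1, T2 and T3.

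The same section places T0 before treatment: "The intervention will begin on the day after T0". It gives the purpose of the T3 visit as measuring safety aspects, namely "somatic complaints/side effects as well as gastrointestinal symptoms".

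The section Secondary outcomes describes the measure in terms of presence: "the presence of somatic complaints/side effects or gastrointestinal symptoms (via the Bristol Stool Scale) will also be evaluated".

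The section Statistical analysis plans general linear models for continuous outcomes "while controlling for baseline assessment, gender, diagnostic group, and center", and generalized linear models for categorical outcomes with no baseline term stated. It also plans repeated-measures models of change from baseline to the follow-up visit within the experimental group.

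**The concern.** A complaint recorded at T1, T2 or T3 may have started after the first sachet or may have been there beforehand. Without the same questions at T0 the two cannot be separated item by item for a participant. Pre-existing complaints enter both arms equally in expectation, so they do not create a false difference. They do shrink a true one and add noise. In a safety comparison, that loss errs towards missing a tolerability problem.

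The schedule itself creates the gap. A later analysis plan can choose a model, but it cannot supply a measurement that was never taken.

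**Working it through.** **1. Reading the schedule.** The section Secondary outcomes in Table 3 has 20 rows. Nineteen carry a T0 mark; the body-system questions do not.

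| Row | Screening | T0 | T1 | T2 | T3 |
|---|---|---|---|---|---|
| Somatic complaints/side effects | – | – | X | X | X |
| Gastrointestinal symptoms | – | X | X | X | X |

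Dosing begins after T0, so the first row has no pre-treatment assessment and the second has one.

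**2. Against the planned analyses.**
- Change from baseline to follow-up in the experimental group: not possible for this measure under any scoring.
- Baseline-adjusted general linear model: not possible if the measure is scored continuously.
- Generalized linear model for presence or absence: can be run, since no baseline term is stated for categorical outcomes.

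**3. Illustrative size, presence/absence.** The article gives no figure to reproduce here. The 90 per arm is 180 / 2 under 1:1 allocation, with no dropout. All complaint rates are assumptions: new complaints in 10% (placebo) versus 30% (synbiotic) of those clear at baseline, and a pre-existing rate b equal in both arms, with every pre-existing complaint persisting.

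Without a baseline, the observed rate in an arm with new-complaint rate i is b + (1 − b)i, so the difference between arms is (1 − b)(0.30 − 0.10):
- b = 0: 0.10 vs 0.30, difference 0.20
- b = 0.2: 0.28 vs 0.44, difference 0.16
- b = 0.4: 0.46 vs 0.58, difference 0.12

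With a T0 assessment, new complaints are counted among those clear at T0, on average 90(1 − b) per arm (90, 72, 54), and the difference stays 0.20.

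Power was simulated (20,000 replicates, two-sided 5% z-test on two proportions):

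| b | Without T0 | With T0 |
|---|---|---|
| 0 | 93% | 93% |
| 0.2 | 62% | 87% |
| 0.4 | 35% | 76% |

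Hand check by power = Φ[(d − 1.96·SE₀)/SE₁], where d is the difference, SE₀ uses the pooled proportion and SE₁ the separate ones:
- b = 0.2, without T0: SE₀ = √(2 × 0.36 × 0.64 / 90) = 0.0716; SE₁ = √((0.28 × 0.72 + 0.44 × 0.56) / 90) = 0.0706; Φ(0.28) = 61%.
- b = 0.2, with T0 (72 per arm): SE₀ = √(2 × 0.20 × 0.80 / 72) = 0.0667; SE₁ = √((0.10 × 0.90 + 0.30 × 0.70) / 72) = 0.0645; Φ(1.07) = 86%.

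Both agree with the simulation to within about 2 percentage points.

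**4. Bias.** With no treatment effect (10% in both arms), the simulated comparison without a baseline gave a mean difference of about 0.000 and a type I error of 4.8% to 5.3%. The missing T0 value costs power, not validity.

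**5. If the measure were a continuous score.** Baseline adjustment leaves a share 1 − r² of the outcome variance, where r is the baseline-to-follow-up correlation: 0.91, 0.75 and 0.51 for an assumed r of 0.3, 0.5 and 0.7. At r = 0.5, 1/0.75 = 1.33, equivalent to about one third more participants. The article gives no such score, so this is conditional.

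**The case against.** The strongest reply is that little is lost. The trial is randomized, double-blind and placebo-controlled, so background complaints balance in expectation. Other safety information exists: gastrointestinal symptoms have a T0 value, adverse events are asked about at each visit (section Criteria for discontinuing allocated interventions), and the clinician takes medical history at T0. Table 1 excludes major physical illness and somatic disorders that the investigator thinks could confound the safety assessments. The questions themselves are not shown and might ask about onset.

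Much of this stands, and it rules out three stronger readings that a reader might infer.

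- *That this is the main tolerability measure.* The article names two safety aspects for T3 and ranks neither first.
- *That treatment effects cannot be told from existing complaints.* At group level they can, with less precision. Only the individual-level separation is lost, and adverse-event enquiry and medical history recover part of it.
- *That the planned model cannot be run.* The article describes presence, and the model for categorical outcomes can be run without a baseline.

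Nor does the background remark on an "overrepresentation of gastrointestinal symptoms in patients with both neurodevelopmental and neuropsychiatric disorders" show that many somatic complaints will predate dosing. It concerns gastrointestinal symptoms, which do have a T0 assessment.

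The objection does not remove the gap. Nothing in the article shows that medical history or the adverse-event enquiry uses the same questions, so complaints new or worse since T0 cannot be scored from them item by item. The exclusions reduce minor complaints but do not abolish them. The label side effects presupposes a dose, but the row also covers somatic complaints, which can exist before one.

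**Conclusion.** The point holds as a design gap with a cheap remedy. It does not bias the between-arm comparison and does not touch the primary outcome. One named safety measure lacks a pre-treatment value. Complaints new or worse since baseline therefore cannot be identified with it, its change from baseline cannot be analysed, and the comparison between arms is diluted to the extent that complaints predate dosing.

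The size is not fixed by the document. In the illustration, power falls from 93% to 62% or 35% with pre-existing complaints in 20% or 40%; a T0 assessment would hold it at 87% or 76%. These figures rest on assumed rates and full persistence of earlier complaints. They shrink if such complaints are rarer, and vanish if there are none. They should be presented only as an illustration.

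**What to change.** Add the body-system questions at T0, before the first sachet, for all participants still to be enrolled. Report by arm the complaints that are new or worse than at T0, and include the T0 value as a covariate where available.

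The cost is a few minutes in a T0 visit that already lasts about 3 hours, and one CRF page. Participants already randomized will lack the value; the first was randomized on 27 February 2019 and recruitment was expected to end on 1 April 2021 (section Trial status), so the benefit falls as enrolment proceeds. The missing values depend on the date of enrolment rather than on treatment. The tabulation of new or worse complaints can therefore be limited to those with a T0 value, while the comparison of complaints on treatment keeps all participants.
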